### Procedures

At the time of recruitment (t_0_) (14 to 24 weeks gestation), participants will complete a screening survey to determine their eligibility. At 24 weeks gestation (t_1_), eligible participants will enroll in the study and complete a baseline survey to assess demographic characteristics and secondary outcome measures. Both researchers and participants will be blinded to group assignment at the baseline assessment and during the educational intervention. All participants will receive an individual 30-minute educational intervention on sleep hygiene during pregnancy delivered by a study registered nurse at enrollment. The focus on the sleep education will be to provide tips on how to achieve a better night’s sleep during pregnancy such as managing pregnancy weight gain with aerobic activity and keeping a consistent schedule. Participants will also receive a sleep hygiene brochure, adapted from a Massachusetts Lung and Allergy sleep clinic sleep hygiene brochure to include information specific to pregnancy. We piloted the development of the brochure through an online survey that asked about the usefulness of the information and overall aesthetics. We used similar recruitment approaches (ie, Facebook) and eligibility criteria to identify women in the brochure development pilot as will be used for the pilot intervention to ensure the feedback is appropriate for the target population. Based on the participant feedback, we made modifications to the brochure’s graphical design; the information content was deemed useful. After completing the baseline survey and sleep hygiene education, participants and researchers will be unblinded to the group assignment (t_2_). Assignments will be made prior to the start of recruitment by randomizing study identification (ID) numbers into intervention or control group using Web-based randomization software [27]. The results of the randomization process will be placed into individually sealed envelopes labeled with study ID numbers. At t_2_, the study nurse will open the envelope for the ID number assigned to the participant and reveal group assignment. Those in the intervention group will then receive the intervention.

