At 36 weeks gestation (t_3_), all participants will complete an in-person follow-up survey to assess the same secondary outcome measures as at t_1_. Participants will also complete a brief qualitative interview to determine their satisfaction with the sleep hygiene education and, for those in the intervention group, the self-monitoring intervention. Participants will complete a final follow-up phone survey approximately 2 to 4 weeks after delivery (t_4_).

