#### Retention

Retention may be a challenge due to the longitudinal nature of the study. Each participant will be asked to provide multiple contact methods. Increasing incentives will be built into the study at each data collection time point ($20, $30, and $40 gift cards) to encourage retention for both the intervention and control groups. Participants in the intervention arm will keep the Shine 2 device at the study end. Participants in the control arm will be offered a Shine 2 at the study end. The ability to successfully contact participants, deliver the intervention, and collect data at each time point will be recorded to calculate the percentage of participants retained.

To evaluate participant retention with the intervention protocol, the study team will take two actions. First, we will track sleep data weekly for each participant by viewing their sleep log in the study Gmail account. Then, if a lack of data in the sleep log suggests that the participants are not wearing the monitor daily, we will call the participants to find out why they are not using the device, help them problem solve any issues, and encourage them to continue with study adherence.

**Table 1 table1:** Schedule of study assessments for primary and secondary outcomes.

Characteristics			Assessment			
			Screening/enrollment	Baseline	Active intervention	
			t_0_	t_1_	t_2_	t_3_

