### Data Analysis

We will use descriptive statistics to determine the feasibility and acceptability of the pilot intervention. Specifically, we describe recruitment and dropout rates in each group and noncompliance with the intervention among the intervention group only. To assess noncompliance we will use data from the IFTTT applet to determine the proportion of days the monitor was worn during the study period. High compliance will be defined as wearing the monitor at least 80% of days during the study period.

Qualitative methods will be used to determine the acceptability of the intervention, using a qualitative descriptive design [43,44]. The audio recorded interviews will be organized using NVivo 11 (QSR International Inc) software. Recordings will be professionally transcribed verbatim, and transcripts will be checked for accuracy. Descriptive coding will be used to identify and link comparable content and categorize data at a basic level [43]. For further analysis of descriptive codes, content analysis will be used to describe patterns and summarize findings in the data [44]. Memos will be written throughout the analytic process to capture the analysis process and the researchers’ responses to the data. Trustworthiness will be determined through peer debriefing between the research assistant and the principal investigator and the audit trial of documentation of the analysis, including coding, memos, and findings.

To examine the preliminary efficacy of the intervention, all secondary outcome variables will be modeled as continuous outcomes. We will compare baseline characteristics of the intervention groups to ensure randomization was successful. We will present the mean and standard deviation or median and interquartile range for each secondary outcome at baseline and postintervention. A paired *t* test will be used to compare baseline and postintervention means separately in each group. A Student *t* test will then compare the change in each measure between the two intervention groups. Finally, we will calculate within and between-group effect sizes using Cohen d (M_ΔI_ – M_ΔC_ / SD_pooled I and C;_ M_t2_ – M_t3_ / SD_pooled t2 and t3_).

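### The within-group Cohen d is written with t2, when no secondary outcome is measured, and the between-group d leaves its standard deviation undefined

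*Protocol article*

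**What the plan says.** The Data Analysis section plans three steps for the secondary outcomes.

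- Within each arm: "A paired *t* test will be used to compare baseline and postintervention means separately in each group".
- Between arms: "A Student *t* test will then compare the change in each measure between the two intervention groups".
- Effect sizes: Cohen d between groups, "M_ΔI_ – M_ΔC_ / SD_pooled I and C", and within groups, "M_t2_ – M_t3_ / SD_pooled t2 and t3".

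The Procedures section fixes the time points. At t1 (24 weeks) participants "complete a baseline survey to assess demographic characteristics and secondary outcome measures". The step called t2 comes later: "After completing the baseline survey and sleep hygiene education, participants and researchers will be unblinded to the group assignment (t_2"). At t3 (36 weeks), "all participants will complete an in-person follow-up survey to assess the same secondary outcome measures as at t_1". Table 1, titled "Schedule of study assessments for primary and secondary outcomes", marks all five secondary outcome rows at t1 and t3. The only row it marks at t2 is allocation.

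**The concern.** The article goes as far as printing formulas, and they do not fit its own schedule. The within-group formula calls for a mean and an SD at t2, and no secondary outcome is collected then. The between-group formula names its numerator, a difference in mean change, but not its standardiser: the SD pooled over the two arms could be that of change scores, or that of raw scores at some unnamed time.

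The trial states that it is underpowered for group differences and looks for trends and hypotheses. Standardised effects are therefore one of the main summaries for its preliminary-efficacy aim, and the results are meant to inform a grant application for a larger trial. The article also reports that data collection is complete. An open denominator could thus be settled after the data are in hand, and a reader of the results could not tell which scale a given d is on.

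**Working it through.** The plan states no effect size, SD or correlation for the secondary outcomes, so there is no figure of its own to reproduce. The check has four parts.

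**1. Time points.**

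| Step | What happens | Secondary outcomes? |
|---|---|---|
| t1 | Baseline survey, 24 weeks | Yes (Procedures, Table 1) |
| t2 | Unblinding and allocation, after the survey and education | No (Procedures, Table 1) |
| t3 | Follow-up survey, 36 weeks | Yes (Procedures, Table 1) |

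Read literally, the within-group formula has no data for its first mean or for half of its pooled SD. With t1 in place of t2, every term is collected. The between-group formula contains no t2.

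**2. Scale of the between-group d.** Assume equal SDs at t1 and t3 and a within-person correlation r. Then

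SD(change) = SD(raw) × √(2(1 − r)),

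so d on the change-score SD equals d on the raw SD × 1/√(2(1 − r)).

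| r (assumed) | SD(change)/SD(raw) | Multiplier on d | True difference of 0.5 raw SD reported as |
|---|---|---|---|
| 0.3 | 1.183 | 0.85 | 0.42 |
| 0.5 | 1.000 | 1.00 | 0.50 |
| 0.7 | 0.775 | 1.29 | 0.65 |
| 0.8 | 0.632 | 1.58 | 0.79 |

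A worked case with assumed values: mean changes of −2.0 (intervention) and −0.5 (control), raw SD 3. Taking later minus earlier, the within-group values are −2.0/3 = −0.667 and −0.5/3 = −0.167. On the raw SD the between-group d is −1.5/3 = −0.50, exactly the difference of those two. On the change-score SD it is −0.42 at r = 0.3 and −0.79 at r = 0.8.

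**3. Sign.** The within-group formula subtracts later from earlier, so a fall in score is positive: +0.667 and +0.167 in the example. The article does not define the direction of Δ. If Δ is later minus earlier, the same benefit appears as −0.50 between groups. Higher is stated to be worse for sleep disturbance, sleepiness, fatigue and depressive symptoms, whereas for sleep duration the aim is an improvement, so the sign of benefit differs by outcome.

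**4. Precision at the target of 10 per arm.** The small-sample correction is J = 1 − 3/(4 × 18 − 1) = 0.958. For an illustrative d of 0.38, SE = √(2/10 + 0.38²/40) = √0.2036 = 0.451, and 0.38 ± 1.96 × 0.451 gives −0.50 to 1.26. That SE applies when the standardiser is the SD of the quantity compared. For a baseline-adjusted effect on the t1 SD, the first term shrinks by about (1 − r²):

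- r = 0.3: SE = √(0.2 × 0.91 + 0.0036) = 0.431, interval −0.46 to 1.22.
- r = 0.8: SE = √(0.2 × 0.36 + 0.0036) = 0.275, interval −0.16 to 0.92.

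The value 0.38 also appears under Conceptual Framework, as a pooled effect for healthy-eating and physical-activity interventions. It is used here only for scale and is not a forecast for sleep.

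**The case against.** The strongest defence is that no analyst would be misled about t2. The same paragraph says in words that the comparison is of baseline with postintervention means, and only one pre-intervention measurement exists. Since t2 is when the device is handed over, t2 to t3 may be shorthand for the intervention period. This stands: the slip has one evident correction. It is still worth making, because the education session falls between t1 and t2, so a t1-to-t3 change within an arm includes any effect of the education.

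A reader might infer that the effect sizes cannot be computed at all. The article does not support that, since the between-group formula does not use t2 and the within-group formula becomes computable once the label is corrected.

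A reader might also infer that the plan puts the two effects on different scales. That is only one reading. With a raw-score SD they share a scale. With a change-score SD, which fits the preceding t test on change, the scales differ unless r = 0.5, and a different standardiser is acceptable if declared. What the text supports is ambiguity.

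Three further defences hold in part.

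- The missing brackets in the printed formulas may come from typesetting or text extraction, and nobody would compute d that way. They carry no weight here.
- The opposite signs arise only under one direction of Δ, so this is an undefined convention and not a contradiction.
- A condensed article may leave Hedges g, intervals and baseline adjustment to a fuller plan. They belong to the remedy and are not themselves a defect.

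On impact, the article already urges caution and nowhere says that d will size the next trial. It also promises means and SDs, or medians and interquartile ranges, at both times. Where means and SDs are shown, a raw-scale d can be recomputed.

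**Conclusion.** The point holds in two parts. First, the within-group formula names a time point at which the schedule collects no secondary outcome. This is certain, and the intended reading is obvious. Second, the between-group standardiser is undefined. The ambiguity is certain, but its size is conditional: a change-score SD gives about 0.85 to 1.58 times the raw-scale d for r from 0.3 to 0.8, and no difference at r = 0.5. The range rests on assumed correlations and on equal SDs at t1 and t3, neither of which the article gives.

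Severity is minor to moderate. These are descriptive secondary results in a feasibility pilot that admits it lacks power. The matter would grow only if d were carried into planning without its scale: required sample size varies with 1/d², so a factor of 1.58 in d is a factor of 2.5 in n.

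**What to change.** Replace the formula line with definitions to this effect:

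- Change is t3 minus t1 throughout, with t1 in place of t2 in the within-group formula and brackets around both numerators.
- Within-group and between-group effects are both divided by the t1 SD pooled over the two arms.
- The between-group effect is adjusted for the baseline value of the outcome.
- The direction of benefit is stated for each scale, including sleep duration.
- The between-group effect is reported as Hedges g with a 95% CI.

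No new data are needed, since t1 and t3 values are already collected. The cost is a revised formula line and one baseline-adjusted model per outcome. The reported values may move either way. Compared with a change-score SD, the t1 SD would lower d by about 37% at r = 0.8 (0.632 times) and raise it by about 18% at r = 0.3 (1.183 times). The small-sample correction takes off a further 4% or so. The intervals will make the estimates look imprecise, which at 10 per arm they are.

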## Results

Recruitment for this study began in September 2017 and ended in March 2018. Data collection for the primary and secondary aims was completed in August 2018. We anticipate that the data analysis for primary aims, evaluating the feasibility and acceptability of the intervention, will be completed by July 2019. We anticipate that the data analysis on the secondary aims, examining the preliminary efficacy of the trial on sleep quality and duration, sleep disturbance, excessive daytime sleepiness, fatigue, and depressive symptoms, will be completed by December 2019. The results from this trial will inform the development of a larger National Institutes of Health grant application to test the efficacy of an enhanced version of the sleep intervention that we plan to submit in the year 2020.

## Discussion

### Principal Findings

This 12-week, parallel arm, pilot randomized controlled trial proposes to establish the feasibility and acceptability of conducting a 12-week intervention for sleep self-management among pregnant women using a PHM device and determine the feasibility of collecting data on sleep and physical activity using a PHM device. Secondarily, the trial will determine the preliminary efficacy of the trial on improving self-reported sleep quality and nocturnal sleep duration and decreasing sleep disturbances, excessive daytime sleepiness, fatigue, and depressive symptoms. This study is novel because it will be the first to apply a PHM device as a tool for promoting self-management of sleep among pregnant women. We anticipate that at least 80% of participants will wear the PHM device daily throughout the study period and report high satisfaction with the intervention. Further, we anticipate that participant feedback will inform the design of a larger randomized controlled trial aiming to improve sleep quality and duration during pregnancy using a PHM device.

Specifically, findings from the pilot study will inform the recruitment and intervention implementation, including strategies to increase adherence. As far as refining our recruitment plan, we will learn important information about the demographic characteristics (eg, race and ethnicity, socioeconomic status, baseline sleep characteristics) of the sample population. Our recruitment goal is for at least 20% of the sample to come from racial and ethnic minority groups. If we fail to recruit a racial and ethnically diverse sample, we will identify specific recruitment barriers and refine our recruitment strategy. Second, we will identify which recruitment approach (eg, Facebook, flyering at local clinics) is the most cost effective. Third, identifying weekly and monthly recruitment yields will allow us to determine if our recruitment strategy could feasibly enroll participants for an adequately powered study. We will need to consider the length of the recruitment period, adding clinical sites, and budgetary considerations for the larger trial.

In addition to recruitment, participant adherence is another critical challenge this feasibility study will help inform. Since previous studies did not use a PHM device specifically to monitor sleep, we would like to first address if pregnant women will wear them for this purpose. Through the IFTTT app, we will be able to identify when the monitor is not worn and elicit feedback from participants on any barriers to wearing the device. If specific benchmarks for retention are not met (>80%), we will refine our current approach (eg, incentive, engagement strategies) to address any challenges that exist.

Last, this feasibility trial will provide important information about the implementation of the intervention. The intervention was meant to be a low-contact intervention to be consistent with the limited time resources in a clinic setting. Through the participant satisfaction interview, we will determine whether the initial counseling session and sleep brochure address challenges specific to pregnant women. Concerning the instruments for the intervention (Shine 2), we will learn if there are specific features participants liked or did not like about the device and the extent to which participants used the device to self-monitor their sleep. Identifying specific features will allow us to be responsive to rapid changes in technology, steering us to select a device that contains features participants find particularly helpful. More generally, we will learn if wearing the PMH device serves as a motivator to participants to monitor their sleep more closely and identify behaviors affecting their sleep.

Given the prevalence and morbidity of sleep disturbances during pregnancy, it is essential to identify cost-effective approaches to promote better sleep in this group. Wearable devices have the potential to facilitate behavioral interventions as they include theory-driven self-regulatory techniques such as behavioral self-monitoring. There has been increasing interest in incorporating PMH devices into clinical settings. For example, PHM devices have been used to monitor inpatient recovery [45]. In an outpatient care setting, PHM devices can be used to track health behaviors remotely and monitor progress toward meeting patient-centered goals around sleep [46,47]. Data from PHM devices can be integrated into electronic medical records. For the patient, tracking behavior more closely can help the patient identify patterns and make choices to change behavior to improve sleep [48]. No prior studies have used a PHM to promote sleep during pregnancy; therefore, novel intervention strategies need to be developed and refined.

### Limitations

This study will, however, have important limitations that warrant discussion. First, the study requires that participants have access to mobile phones compatible with the study monitor; therefore, individuals of low socioeconomic status may potentially be excluded from the study [49]. However, lower income Americans have made gains in technology adoption including the use of mobile phones, which is likely to continue in the future. In addition, since there are multiple components of the intervention (ie, PHM and follow-up calls), we will not be able to discern which component explains differences between the groups, if any are observed. We will keep the follow-up calls briefs and use them primarily as a method of collecting information on the study’s feasibility throughout. However, we won’t be able to remove the potential effects repeated contacts can have on a participant’s ability to change behavior. Third, we will not exclude participants based on their use of any PHM. Therefore, control group participants may have access to a PHM during the study. However, none of the participants will be using our specific study monitor at baseline. Further, participants in the control group will receive study monitors at the end of the study to reduce attrition and limit the use of PHMs during the study. Last, due to the small sample size, we will not have sufficient power to detect any group differences in the secondary outcomes. Therefore, any significant or nonsignificant findings must be interpreted with caution. We will, however, be able to observed trends and generate hypotheses to be tested in a fully powered study.

### Conclusion

This pilot feasibility study will provide the foundation for a larger trial that aims to improve sleep during pregnancy using a PHM device. The findings from this feasibility and acceptability pilot will provide valuable feedback on the design and implementation of the intervention.

## Abbreviations

ID: identification
PHM: personal health monitor
PSQI: Pittsburgh Sleep Quality Index
